# Vincular Project: study protocol for a randomized controlled trial with changes in 24-h movement behaviors targeting the reduce of depressive symptoms in adults

**DOI:** 10.1186/s13063-026-09771-8

**Published:** 2026-05-15

**Keywords:** Adults, 24-h movement behaviors, Depression, Clinical trial, Basic psychological needs, Protocol

## Abstract

**Background:**

A better understanding of how behavior change interventions work to reduce depressive symptoms, as well as their effects and potential mediators, is needed. This paper described the methods of the Vincular Project, an intervention based on Self-Determination Theory with changes in 24-h movement behaviors (physical activity, sedentary behavior, and sleep) to reduce depressive symptoms in Brazilian adults.

**Methods:**

This is a randomized, controlled, blinded clinical trial with adults aged 20 to 59 years, of both sexes, with depressive symptoms. The sample was intentional and non-probabilistic and participants were allocated to a control group and an intervention group. The intervention was carried out twice a week, for 16 weeks, and consisted of face-to-face and online meetings. The activities aimed to make participants more aware of their living and health conditions, exploring 24-h movement behaviors, especially physical activity, and their relationships with depressive symptoms. The contents were different in each meeting and the activities were organized into four blocks, the first being contextualization, the second with general and specific guidelines on 24-h movement behaviors, the third with opportunities to practice physical activity in different contexts and situations, and the fourth with strategies for maintaining healthy behaviors in the short and long term. Baseline (January 2023), post-intervention (May 2023), and maintenance (November 2023) evaluations included depressive symptoms as primary outcome, and 24-h movement behaviors and basic psychological needs as secondary outcomes. The variables of autonomy, competence, and relatedness were also tested as mediators related to the effectiveness of the intervention on depressive symptoms. Depressive symptoms were measured by the Patient Health Questionnaire-9 (PHQ-9), 24-h movement behaviors by self-report and accelerometry, and basic psychological needs by the translated and adapted version of the Basic Psychological Needs in Exercise Scale (BPNES). To verify the effect of the intervention, per-protocol and intention-to-treat analyses will be conducted using generalized estimating equations (GEE). Structural equation models (SEMs) will be employed in the mediation analysis.

**Discussion:**

The results of this trial will involve valuable information about the effect of a behavioral intervention to reduce depressive symptoms carried out in a middle-income country.

**Trial registration:**

Brazilian Registry of Clinical Trials (ReBEC): RBR-7466htj. Approved 14 April 2023, https://ensaiosclinicos.gov.br/rg/RBR-7466htj

**Supplementary Information:**

The online version contains supplementary material available at 10.1186/s13063-026-09771-8.

## Introduction

Currently, depression represents one of the biggest causes of disability, being the disorder with the greatest impact on the global burden of disease [1, 2] and being associated with a higher rate of premature mortality [3, 4]. This chronic non-communicable disease affects more than 300 million people of all ages, which is equivalent to approximately 4.4% of the population globally [1, 2], generating a high cost to the global economy [5]. Considering that depression is often underdiagnosed and undertreated [5, 6], there is a need for specific interventions that can contribute to a more stable remission, prolonging the time between depressive episodes and reducing relapse rates, as well as monitoring their indicators to better control this scenario.

Although psychotherapy and pharmacotherapy are the most recognized treatments for depressive symptoms and depression [7, 8], recent evidence highlights that regular physical activity can be considered an additional, effective, and independent option [9–12]. This is because aspects related to lifestyle—which are modifiable—are strongly associated with depressive episodes [13–17]. Along with physical activity, sedentary behavior and sleep, known as 24-h movement behaviors, have been gaining notoriety in the context of mental illnesses, mainly due to the fact that these behaviors contribute simultaneously to the prevention and treatment of depression and depressive symptoms, for example [13, 14, 16].

Systematic reviews and meta-analysis studies confirm the hypothesis that physical inactivity [18, 19], high sedentary behavior [20, 21], short and long sleep duration [22], and sleeping problems, such as insomnia [23, 24], are associated with greater chances of developing depression. However, the reverse direction of these associations may also occur, suggesting that individuals with depressive symptoms are more likely to be physically inactive or not meet physical activity recommendations [13, 15, 16, 19], to present high levels of sedentary behavior [13, 16], and to develop sleep disorders [14, 17], in compared to those without a diagnosis of this disease. As for clinical trials investigating these behaviors and depressive episodes, it is possible to see positive results, with physical activity providing antidepressant effects on the disease [19] and sleep bringing improvements in general mental health, depression, and other mental health problems, such as anxiety, stress, and rumination [14]. For sedentary behavior, what generally occurs is the development of interventions in which physically active participants are exposed to a reduction in the physical activities they usually do for, approximately, 1 week with the purpose of examining the effect of these changes on symptoms of mood, stress, and depression [25–27].

Furthermore, little is known about the long-term effects of these interventions. In addition to the heterogeneous data on monitoring and maintenance [28], there is a lack of studies regarding the remission of depression symptoms and the continuity of healthy behaviors [29]. Although short-term results can be achieved for both depressive symptoms [9, 11, 12] and 24-h movement behaviors [14, 19, 25], it is crucial to emphasize the significance of investigating these variables in the long term, months after the interventions have concluded. This approach is essential for filling critical gaps in understanding the enduring impacts of these interventions. Despite the benefits of a healthy lifestyle, individuals with depressive symptoms experience barriers such as the inherent symptomatology of the disease, leading to a lack of motivation and loss of interest [2], common factors for discontinuation of health promotion efforts across various contexts.

In this sense, the implementation of resources that address multicomponent actions, related to the integrated management of 24-h movement behaviors, and that adopt adherence and maintenance strategies may be a more effective method compared to traditional trials, which involve segmented approaches to these behaviors, in an attempt to reduce symptoms of depression in the adult population. Moreover, considering the low adherence of this population to programs of this nature [30, 31] and given that these behaviors are influenced by several factors, such as sociodemographic, lifestyle, and health conditions [16], it is also necessary to understand the mechanisms that can trigger psychological aspects that favor behavior change processes.

For this purpose, Self-Determination Theory, for instance, contributes to a better understanding of the different types of motivation that lead individuals to either adopt or refrain from certain behaviors [32]. The more autonomous (or self-determined) an individual is, the more adaptive the health outcomes, favoring behavioral adoption and maintenance [32, 33]. Additionally, it is observed that more autonomous motivation is facilitated by the satisfaction of three basic psychological needs, including autonomy (feeling empowered and having the power of choice), competence (feeling capable and effective), and relatedness (feeling connected, close, and valued by others) [32, 34]. Whether an individual’s psychological needs are met or not depends mainly on the extent to which the environment and relationships support or frustrate these needs [34, 35]. Thus, when considering interventions aimed at behavior change with a focus on reducing depressive symptoms, it is evident that the satisfaction of basic psychological needs can be considered an important mediator in the relationship between the proposed programs and the investigated outcomes [36]. Nevertheless, there remains a challenge for healthcare professionals in facilitating the satisfaction of these needs more effectively, particularly concerning techniques and strategies [37], especially in mental health outcomes.

In light of the above, the objective of this paper is to provide a step-by-step description of the design of Vincular Project, a behavior change intervention based on Self-Determination Theory for the reduction of depressive symptoms in Brazilian adults. The intervention is grounded not only in the main outcomes (depressive symptoms and 24-h movement behaviors) but also in potential mediating factors (basic psychological needs) and health-related outcomes (e.g., lifestyle), as well as assessment of maintenance of long-term effects.

## Methods

### The Vincular Project aim and study design overview

Considering that the intervention proposal addressed aspects of both the body and mind, in addition to the constructs of the Self-Determination Theory, the project was named “Vincular” (the Portuguese word for “to link” or “to connect”), in the sense of intertwining, connecting, and incorporating all these elements. Additionally, the word ends in “lar” (which, when translated into English, means “home”), precisely representing the intended creation of a welcoming, safe, receptive environment free from judgment. The main objective was to promote different dynamics based on the Self-Determination Theory, with a focus on 24-h movement behaviors, especially physical activity, to reduce depression symptoms in adults from Florianópolis, a city located in the southern region of Brazil. Furthermore, as secondary objectives, the study aimed to investigate the effects of the program on indicators of 24-h movement behaviors (physical activity, sedentary behavior, and sleep) and on basic psychological needs (autonomy, competence, and relatedness), as well as verifying its role mediator in achieving primary results.

The recommendations of the SPIRIT (Standard Protocol Items: Recommendations for Interventional Trials) were followed to guide the construction of the present study [38]. The Vincular Project is a parallel-group, randomized controlled clinical trial with blinding of the primary, secondary outcomes, and other variables, following the design outlined by Hulley et al. [39]. It consists of two arms (a control group and an intervention group) and is conducted at a single center. This study was registered in the Brazilian Registry of Clinical Trials (ReBEC) under the identification code RBR-7466htj, and submitted to the Research Ethics Committee involving Human Subjects at the Federal University of Santa Catarina (CEPSH-UFSC), obtaining a favorable opinion (Opinion Number 5.622.082; CAAE 60378122.1.0000.0121). The informed consent form was made available online, accessible for download, and participants indicated their agreement or disagreement to participate in the research.

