### Sample size, randomization, and allocation concealment

The sample size was calculated using G*power 3.1.9.2 software, and was based on an ANOVA model for repeated measures with three time points and two groups. Parameters included an average effect size of 0.25, statistical power of 80%, and 5% significance level for two-tailed tests, reaching a value of 28 individuals. Anticipating a potential dropout rate of up to 50%, the number calculated was doubled, bringing the total sample size to 56 individuals. Eligible individuals were randomly assigned to either the control group (CG), instructed to maintain their usual activities, or the intervention group (IG), which actively participated in the program. To ensure numerical and participant characteristic balance between groups, randomization was stratified by sex, age, and PHQ-9 score, employing a 1:1 ratio. The randomization process was executed using the online platform randomizar.org by researchers not directly involved in the intervention. The allocation list was concealed from all study evaluators.

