### Experimental procedure

The intervention was carried out twice a week, on alternate days, spanning a total duration of 16 weeks. To enhance communication and enable active participation in meetings, promoting conversational dynamics and practical engagement, the IG participants were divided into two groups. The sessions, lasting approximately one and a half hours, were conducted both in person (80%) and online (20%), using the Google Meet platform. All meetings were based on the Self-Determination Theory and involved activities conducted by professionals in the field of Physical Education, affiliated with UFSC, along with the participation of external guests. These professionals were tasked, through the proposed dynamics, to support the basic psychological needs of the participants. This influence on the quality of motivation for behaviors and the level of participation/involvement in these behaviors has the potential to bring about changes in mental and physical health outcomes. In all meetings, professionals sought to implement the classification system of techniques constituting interventions based on Self-Determination Theory, as developed by Teixeira et al. [36]. The organizing principle of this system revolves around the satisfaction of psychological needs within healthcare contexts. According to the authors, each technique targeted the construct most closely related to psychological need satisfaction (autonomy, competence, or relatedness), with the aim of achieving a heightened level of motivation and promoting behavior change. In Fig. 2, it is possible to visualize the basic process model of the Self-Determination Theory that was developed in the intervention program.

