Meeting 32: Project closing: trail □ [15–17]	To provide moments of reflection on the trajectory of the intervention and future prospects	Trail on the Costa da Lagoa (Florianópolis/SC)	- Send a statement about your experience with the project, with your perceptions of the issues addressed in the intervention	Autonomy: orientation with intrinsic objective Competence: provision of encouragement and support Relatedness: cooperation group	- Rationalizing the role of physical activity for reasons such as building a sense of friendship, improvement of skills, energy gain, and a better lifestyle - providing positive feedback to the class and individually, whether recognizing an effort of the participant or complimenting his attitude - Creating groups in virtual environments for experience exchange, facilitating the communication between participants

□: face-to-face meetings; ○: online meetings; 1: Gillison et al. [37]; 2: Brooks et al. [97]; 3: Friedman; Krause-Parello [98]; 4: Kamioka et al. [99]; 5: Nahas [55]; 6: Conn et al. [100]; 7: Laux et al. [101]; 8: Serra; Pimenta; Quemelo [102]; 9: Ekinci; Sanlier [103]; 10: Kris-Etherton et al. [104]; 11: Singh et al. [105]; 12: Bento-Soares; Schiavon [106]; 13: Menegaldo; Bortoleto; Mateu [107]; 14: Menegaldo; Bortoleto [108]; 15: Brito et al. [93]; 16: Coventry et al. [94﻿]; 17: Frühauf et al. [95]

The GC, in turn, was expected to continue with its usual activities. However, recognizing the high chance of participants allocated to this group dropping out the research, a decision was made to maintain contact through telephone messages every 2 weeks. The content of these messages included psychoeducational materials on mental health, as well as guidelines for practicing physical activity, reducing sedentary behavior, and improving sleep, which were also shared with individuals who did not meet the eligibility criteria, as mentioned previously (Table 5). It is also worth noting that, if the effectiveness of the intervention is confirmed, the researchers plan to offer the intervention to the control group later, with the goal of extending benefits to all study participants.

**Table 5 Tab5:** Support materials provided to control group participants

Materials	Description	Access

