Eligible participants subsequently completed a second questionnaire, which incorporated various tools. Although this compilation of instruments was administered online through the Google Form® platform, participants were requested to complete it in the presence of the Vincular Project team, in order to provide assistance when necessary. Some variables were collected using the questionnaire employed in Vigitel telephone surveys, which stands for the Surveillance of Risk and Protective Factors for Chronic Diseases by Telephone Survey, such as (a) sociodemographic information (age, sex, marital status, skin color, and education); (b) behavioral aspects (level of physical activity during leisure time, commuting, domestic, and work); (c) health conditions (from the diagnosis of chronic non-communicable diseases); and (d) self-perceived health. This material was created based on other tools applied by monitoring systems for risk factors for chronic diseases [110, 111] and experiences from system implementation tests carried out in some Brazilian cities [112–114].

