### Trial status

Concluded. Ethics approval: September 2022. Recruitment: November 2022 to January 2023. Allocation: January 2023. The assessment of the variables of interest was carried out at three moments: (a) baseline pre-intervention (January 2023); (b) post-intervention, immediately following the conclusion of the program (May 2023); and (c) post-intervention, 6 months after the end of the intervention (follow-up evaluation, conducted in November 2023). The authors acknowledge the importance of submitting the protocol before the start of recruitment, in accordance with clinical trial guidelines. However, conducting research in Brazil presents significant operational challenges due to limited investment and lack of external funding opportunities. This study did not receive financial support, which prevented the hiring of professionals to conduct interventions involving complex and specialized content related to human movement. Additionally, the research team was restricted, consisting of only two researchers—one master’s and one doctoral student—under the supervision of a single supervisor. Furthermore, the present study does not represent a conventional physical activity intervention, in which variables such as intensity, volume, and duration can be easily manipulated. Instead, it is a behaviorally oriented and interactive approach, requiring continuous engagement with participants. Active and attentive listening played a key role in tailoring physical activity practices to individual preferences and real-life contexts. The dynamic nature of the intervention, aimed at fostering intrinsic motivation and long-term adherence—based on self-determination theory—made it challenging to define rigid protocols in advance, as the intervention was designed to be flexible and responsive to each participant’s needs and motivations. Despite these limitations, participant recruitment only began after approval from the ethics committee, and the intervention was conducted in full compliance with ethical principles, ensuring transparency and proper documentation of all study procedures.

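### The article claims blinded primary and secondary outcomes, but the PHQ-9 and the other outcome questionnaires are self-rated by participants who know their arm

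*Protocol article*

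**What the plan says.** The abstract states: "This is a randomized, controlled, blinded clinical trial with adults aged 20 to 59 years". The design overview under Methods is more specific and describes a "randomized controlled clinical trial with blinding of the primary, secondary outcomes, and other variables". Neither place says who was blinded.

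The section on sample size and randomization gives the one masking step described: "The allocation list was concealed from all study evaluators". The same section sets out the two conditions. Controls were "instructed to maintain their usual activities, or the intervention group (IG), which actively participated in the program". Experimental procedure adds: "The intervention was carried out twice a week, on alternate days, spanning a total duration of 16 weeks", which makes 32 meetings. For controls, "a decision was made to maintain contact through telephone messages every 2 weeks"; no sham or attention-matched programme is described.

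The primary outcome is depressive symptoms on the PHQ-9, in which respondents rate how often they had each symptom. BPNES, SIMPAQ, the sitting-time questionnaire and the PSQI are also answered by the participant. The Assessments section says that questionnaires at all three time points were completed with a trained researcher present. The limitations in the Discussion do not mention unblinded self-report.

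**The concern.** For a self-rated scale the participant is the outcome assessor. If the participant knows the arm, the rating is unblinded, whoever hands over the form. A reader told that the primary outcome is blinded will take a PHQ-9 difference as protected against expectancy and courtesy responding. It is not protected.

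The same weakness reaches the mediation analysis. BPNES is both a secondary outcome and the source of the three mediators. A shared tendency to answer favourably on BPNES and PHQ-9 could therefore appear as an indirect effect. Data collection is finished but the analyses are still described in the future tense, so the label can be corrected before results papers repeat it.

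**Working it through.** The point rests on comparing passages, not on a figure in the plan.

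1. Who rates? PHQ-9 items ask respondents how often they had each symptom (Data collection instruments). BPNES is expressly described as self-report. SIMPAQ, the sitting-time questionnaire and the PSQI ask for the respondent's own account. Rater = participant.
2. Does the rater know the arm? The article never says so in words, but it follows from the conditions: two meetings a week × 16 weeks = 32 meetings, against usual activities with messages every 2 weeks. The two cannot be confused.
3. Does the described masking reach the rater? The list was concealed from evaluators. This could keep the person administering the form unaware of the arm. It does nothing for the person answering it.
4. Which outcomes are affected? Post-allocation PHQ-9, the BPNES scores and the questionnaire versions of movement and sleep. The screening PHQ-9 precedes allocation. Wrist accelerometry is not self-rated, so this argument does not reach it.

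An illustration of what is at stake follows. Shift and SD are assumptions; the document gives neither.

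- Arm sizes: 56 randomized 1:1 gives 28 per arm. After the planned dropout of up to 50%, 28 remain, or 14 per arm.
- Model: two-sample t test, no true effect, and a pure reporting difference b favouring the intervention.
- Non-centrality: δ = (b / SD) × √(n/2), with df = 2n − 2. The chance of a significant result favouring the intervention is P(T > t₀.₉₇₅) under the non-central t. Nominal: 2.5%.
- n = 28 (df 54, critical value 2.005), SD 5: b = 1 gives δ = 0.2 × √14 = 0.748, chance 11%; b = 2 gives δ = 0.4 × √14 = 1.497, chance 31%.
- n = 14 (df 26, critical value 2.056), SD 5: b = 1 gives δ = 0.2 × √7 = 0.529, chance 7%; b = 2 gives δ = 0.4 × √7 = 1.058, chance 17%.
- Extremes: b = 1 with SD 6 to b = 2 with SD 4 gives 9% to 45% at n = 28, and 6% to 25% at n = 14.

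**The case against.** The strongest reply is that the article never says participants were blind. Read with the evaluator concealment, its blinding statements may be a loose description of evaluator blinding, and participant blinding is unattainable in a comparison of this kind. The second half of that stands: self-report in an unmaskable behavioural trial is legitimate. The first half does not rescue the wording, because the design overview attaches the blinding to the outcomes themselves, and the primary outcome is rated by the participant.

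Several stronger readings are tempting but not supported:

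- A reader might infer that the whole blinding statement is false. It also covers accelerometer outcomes, and nothing shows these were processed or analysed unmasked.
- A reader might infer that the team helped participants with the PHQ-9, because "participants were requested to complete it in the presence of the Vincular Project team, in order to provide assistance when necessary". That sentence concerns the second questionnaire, and the instruments listed for it do not include the PHQ-9. The Assessments section, which covers all time points, mentions a researcher's presence but not help.
- A reader might infer that assessors had delivered the sessions, because "the research team was restricted, consisting of only two researchers". Elsewhere the team comprises undergraduate, master's and doctoral students, and sessions were led by Physical Education professionals with external guests. Overlap is plausible, but the article does not say who assessed whom.
- A reader might infer that bias acts in the intervention arm alone. Controls received regular contact, mental-health material and individual activity reports, so they could also respond to attention, which would narrow the difference.

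**Conclusion.** The concern holds for the PHQ-9 and the other questionnaire outcomes: the abstract and design overview claim blinding that the described design cannot provide for them. It does not extend to accelerometry, and it does not establish that assessors were aware of allocation.

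The conclusion needs only that participants could tell a 32-meeting programme from usual activities. It does not depend on the illustrative rates. Those assume a net shift of 1 to 2 points, an SD of 4 to 6 and a simple t test in place of the planned GEE. They show that a modest reporting difference could matter at this sample size, not that one occurred. The error is one of reporting: no estimand, sample size or analysis changes, but the stated protection of the primary outcome is wrong.

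**What to change.** - In the abstract and the design overview, state that participants and intervention staff were not blinded, and that the PHQ-9 and all other questionnaires are unblinded self-report. Limit the blinding claim to what was actually masked: evaluators' access to the allocation list, plus any other masking that really took place.
- In the limitations, add unblinded self-report of the primary outcome and of the mediators.
- In the results reports, qualify the PHQ-9 and mediation conclusions accordingly.

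The cost is a few sentences and a less favourable risk-of-bias statement. No new data or analysis is needed. Data collection ended in November 2023, so neither a change to assessments nor a new ranking of accelerometry over questionnaires is called for.
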